According to the Spanish Ministry of Health’s Survey on Alcohol and Drugs, 33.1% of the country’s population aged ≥15 years still smokes^18^. Smokers are likely to suffer from chronic and acute tobacco-related pathologies, and generate high economic and social costs for the country’s health system^19^. Many will need surgery to treat medical conditions that may or may not derive from their tobacco use.

The need to undergo surgery is associated with a higher probability of successful smoking cessation^20^. But in spite of the opportunity that imminent surgery represents for giving up smoking, tobacco consumption in the pre-surgical period is not an issue that is systematically addressed13. In Catalonia, the identification of smokers who are motivated to give up (and the provision of support for their efforts to do so) does not reach the desired levels^21^. It is clear that effective interventions should be planned at key times such as pre-surgical visits.

The World Health Organization (WHO) urges countries to include smoking cessation programs for pre-surgical patients^22^ as a measure to reduce complications and improve long-term health. In Spain, however, there is no systematic pre-surgical intervention for cessation of tobacco use, nor has any such intervention been evaluated to date. According to the WHO’s ‘Research on the Implementation of Health Policies: a Practical Guide’^23^, applied research is needed to evaluate the effectiveness of interventions, taking into account the real situations of healthcare systems and patients. Conducting studies that demonstrate not just the effectiveness of interventions but also the feasibility of their introduction into real healthcare systems favors their subsequent implementation, sustainability, and dissemination.

The aim of the trial described here is to evaluate the efficacy of an intensive pre-surgical intervention to promote smoking cessation in smokers scheduled to undergo either elective orthopedic surgery with implants or general/urological surgery. These types of surgeries provide sufficient time for preoperative planning and the implementation of a smoking cessation intervention (4 weeks), enabling us to compare the impact across various surgical types and highlight potential differences in outcomes.

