### Sample size and randomization

Every year, approximately 1800 surgical procedures of these kinds are performed at our hospital, of which approximately 25% are carried out in smokers. The sample size has been calculated assuming four equal groups with an estimated difference of 15 percentage points between the predicted rates of abstinence at twelve months in the IG (20%) and the CG (5%). With an expected loss to follow-up rate of 10%, 232 subjects will be needed (58 per group). The sample size has been calculated using the software STATA (StataCorp. 2023. *Stata Statistical Software: Release 18*. College Station, TX: StataCorp LLC). Patients will be assigned to their group by computer-generated random sequence (Stata *ralloc* function) (1:1 assignment) (REDCap). The study will be conducted in a single-blind manner (blinded for surgeons, collaborating researchers, and outcome analysts). There are no circumstances that would necessitate unblinding.

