### Data analysis

The implementation of the intervention will be evaluated with data on fidelity, dose and scope with respect to the protocol (time spent on visits, use of instruments, barriers and problems detected, recruitment of participants, adherence to treatment, satisfaction). This stage will be carried out prior to the analysis of the results of the RCT. The efficacy of the intervention in terms of abstinence and post-surgical complications will be evaluated by comparing IG and CG. The data will be analyzed separately in the two surgery groups (orthopedic with implants and general/urological). Using the data obtained at the beginning of the study (i.e. a questionnaire with baseline data on tobacco consumption and sociodemographic variables) and the data from the different assessments over the course of the study, descriptive analyses will be performed and a contingency table with bivariate analysis will be created. Logistic regression will be performed to assess the efficacy of the intervention and the rest of the outcome variables. As part of our secondary analyses, we will explore whether the intervention effect varies across different surgical groups by including an interaction term (type of surgery × intervention) in our regression models. Considering the longitudinal nature of our data, a generalized linear mixed binomial family model to account for the correlation between repeated measurements within individuals will be used to assess the evolution of smoking cessation. Hazard ratios (HRs) of surgical complications in the IG and the CG will be calculated using Cox regression models. The proportional hazards assumption will be evaluated using statistical tests (e.g. Schoenfeld residuals) to ensure the validity of the Cox model. The number of patients needed to be treated to achieve cessation in one patient (NNT, and its 95% confidence interval) will be calculated over the one-year period. The NNT is the inverse of the attributable risk and is useful for conveying the efficacy of the intervention to patients, managers and clinicians. All analyses will be performed on an intention-to-treat basis. The level of statistical significance will be set at α=0.05 and the Bonferroni correction will be considered to adjust for multiple comparisons.

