## DISCUSSION

Smoking is a major risk for patients undergoing surgery. Surgical complications are associated with smoking increasing readmission rates, prolonging hospital stays and ultimately increasing healthcare costs.

Smokers scheduled for surgery are at an ideal time to try a quit attempt^32^. Intensive interventions initiated at preoperative visits are known to be effective^17^ and can reduce complications. Despite this evidence, little help in this regard is offered during pre-surgical visits^33^. This study is the first in Spain to evaluate the effectiveness of an intensive pre-surgical intervention comprising psychological and behavioral support, pharmacological therapy, and a one-year follow-up program designed to help patients quit smoking before they undergo surgery.

The sample size and stratification will allow us to perform subgroup analyses, and the one-year follow-up period will enable us to obtain longterm abstinence data comparing CO-oximetry measurements made on the day of surgery and at the end of the study.

The main expected result is the achievement of an abstinence rate that is 15% higher among patients in the IG compared to those in the CG, and, at the same time, a reduction in the risk of complications in the IG. The analyses will also consider sociodemographic variables, comorbidities, type of surgery, and surgical variables such as duration and transfusions required. Other important results for comparison between groups will be motivation, dependence, cessation attempts, and reduction in consumption.

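### The planned logistic interaction between surgery type and intervention rests on about three quitters per control cell, so it needs a penalised fit, risk differences beside it, and more modest claims

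*Protocol article*

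**What the plan says.** Data analysis in the protocol article assesses efficacy by logistic regression and analyses the two surgery groups separately. As a secondary, exploratory step it asks whether the effect varies between them "by including an interaction term (type of surgery × intervention) in our regression models". It names no effect scale, test or small-sample method for that term. Limitations relies on the same interaction as a response to possible selection bias.

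On sizing, the article states: "The sample size has been calculated assuming four equal groups". The basis is 12-month abstinence of 20% with the intervention and 5% without, a 15-percentage-point difference, with 10% loss and 58 per group (232 in all). Data analysis also plans a number needed to treat, which is the inverse of a risk difference.

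Two other sections present the design as able to support the comparison. The Introduction describes the choice of surgeries as "enabling us to compare the impact across various surgical types and highlight potential differences in outcomes". The Discussion says: "The sample size and stratification will allow us to perform subgroup analyses". Neither gives a power figure for a difference between surgery types.

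**The concern.** For a binary outcome under logistic regression, the interaction is the ratio of two odds ratios. Its precision depends on the reciprocal of the number of events in each of the four cells, so two control cells with very few quitters dominate the standard error. If either has none, the ordinary maximum-likelihood estimate does not exist as a finite number.

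The analysis that is meant to deliver the comparison claimed in the Introduction and Discussion could therefore return no usable estimate, or an interval too wide to inform anyone. The Conclusions would extend the intervention to the remaining surgical specialties if it proves efficacious, so how far the effect depends on type of surgery bears on how the result is used.

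**Working it through.** **Inputs from the documents.** Four equal cells (two surgery groups by two arms), 58 per cell, 10% loss (58 × 0.9 ≈ 52), abstinence 20% v 5% at 12 months (Sample size and randomization); α = 0.05 (Data analysis).

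**Assumptions.** Two-sided testing; 5% control abstinence in both surgery groups; intervention-group (IG) rates by surgery group as shown below. The documents give only one overall pair of rates.

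**The plan's own figure.** Power and sidedness are not stated, so 232 cannot be uniquely reproduced. Two-sided 0.05 with 90% power gives 101 per arm, 113 after 10% loss and 226 in total, close to 232 with the surgery groups pooled. No variant tried gives 58 per arm within one surgery group; power for 20% v 5% there is 64% at 52 per arm and 69% at 58. The only stated sizing basis is the main effect.

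**Step 1: quitters per control cell.** 52 × 0.05 = 2.6; 58 × 0.05 = 2.9.

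**Step 2: chance of an empty control cell.** P = 1 − (1 − 0.95ⁿ)².
- n = 52: 0.95⁵² = 0.0694, so P = 13.4%.
- n = 58: 0.95⁵⁸ = 0.0510, so P = 9.9%.
- If true control abstinence is 3%, P is 31–37%; at 8% or more it is under 3%.
- If one IG cell is also at 5%, the chance of any empty cell is about 15–19%.

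**Step 3: precision under equal effects (20% v 5% in both groups, n = 52).**
- Var(log ratio of odds ratios) = Σ 1/[n p(1 − p)] = (2/0.0475 + 2/0.16)/52 = (42.1 + 12.5)/52 = 1.05, so SE = 1.02.
- The control cells supply 42.1/54.6 = 77% of the variance.
- The 95% interval multiplies or divides the estimate by exp(1.96 × 1.025) ≈ 7.5.
- On the additive scale, SE = √[(2 × 0.0475 + 2 × 0.16)/52] = √(0.415/52) = 0.089, so the 95% CI is about ±17.5 points. That exceeds the 15-point target effect itself.

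**Step 4: rejection rates by simulation** (20,000 runs per scenario, control 5% in both groups; 52 / 58 per cell; Wald counts tables with an empty cell as non-significant).

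| IG abstinence in the two surgery groups | Difference in effect | Logistic, Wald | Logistic, likelihood ratio | Difference in risk differences |
|---|---|---|---|---|
| 20% v 20% | 0 (null) | 1.2% / 1.7% | 7.3% / 7.5% | 5.2% / 5.6% |
| 20% v 5% | 15 points | 16% / 21% | 30% / 32% | 51% / 56% |
| 30% v 10% | 20 points | 19% / 22% | 26% / 28% | 64% / 69% |
| 35% v 5% | 30 points | 41% / 47% | 54% / 57% | 95% / 97% |
| 45% v 5% | 40 points | 54% / 61% | 64% / 68% | >99% |

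For a 10-point difference (25% v 15%), the risk-difference test has about 20% power (19–23%). Adding 0.5 to the counts in its variance lowers the 30% v 10% figure at 52 per cell from 64% to 62%. A repeat simulation put Wald power for 35% v 5% at 40% with 52 per cell. The 30-point difference is therefore missed between 43% (likelihood ratio, 58 per cell) and 60% (Wald, 52 per cell) of the time.

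**Step 5: what each scale can detect with 80% power (normal approximation).** The logistic Wald test needs a ratio of odds ratios of about 16–24. The risk-difference contrast needs a difference of about 22–28 points.

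**Step 6: a penalised fit.** Firth's penalty always gives a finite estimate. Under equal effects its profile-likelihood test rejects in about 4% of trials. It repairs estimation and calibration; it does not remove the lack of information.

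**Step 7: the two scales are different hypotheses.**
- Control 5% v 10% with a constant odds ratio of 4.75 implies IG rates of 20% v 34.55%, so the risk differences are 15 and 24.55 points. The additive test rejects in roughly one trial in six although the odds ratios are equal.
- Control 5% v 10% with IG 20% v 25% has equal risk differences (15 points each), but odds ratios of 4.75 and 3.0, a ratio of 1.58.

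**The case against.** The strongest reply has four parts.

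1. **Estimation rarely fails outright.** A reader might infer that the term often cannot be estimated. At the planned rates that happens in about 1 trial in 7 to 1 in 10. Even then only the ordinary estimate and Wald test fail; the likelihood-ratio test and a penalised fit still work. The article names no test, so the Wald figures cannot be called the planned analysis. This stands.

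2. **The additive contrast is not a better version of the same test.** A reader might infer from Step 4 that the risk-difference test should replace the odds-ratio term. The power advantage assumes equal control rates, which the documents do not state for each surgery type. Step 7 shows that the scales part company when those rates differ. An interaction on the scale of the main logistic model is conventional. This stands, and low power alone is no reason to demote the odds-ratio term.

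3. **The plan is cautious about this analysis.** It is labelled secondary and exploratory, the surgery groups are analysed separately, and nothing says that a null interaction will be taken as equal effect or will trigger pooling. This stands against any charge that the plan draws that inference. It does not answer the Introduction and Discussion, which present the comparison as something the design and sample size support.

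4. **Details belong to an unseen analysis plan.** Partly fair: penalisation and effect scale are often left there. But the article itself chooses the model and the interaction term, and claims the design can deliver the comparison. Those statements can be checked against its own numbers.

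**Conclusion.** The point holds as a concern about usability and wording. At the plan's own rates the logistic interaction has about 2.6–2.9 quitters per control cell, no finite ordinary estimate in about 10–13% of trials, and miscalibrated standard tests (about 1% for Wald and 7% for likelihood ratio, against 5%). It misses a 30-point difference in effect about 43–60% of the time. The risk-difference contrast does better when control rates are equal, but its power is still only about 20% at 10 points and 62–69% at 20 points.

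The documents do not support saying that the term usually fails, that it would always miss large differences, or that the additive scale is the only right one. Reporting risk differences as well is justified because the plan already sets its target in percentage points and reports a number needed to treat.

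The conclusion assumes the logistic reading of the interaction for 12-month abstinence, two-sided α = 0.05, 5% control abstinence in both surgery groups and the assumed IG rates shown. Empty control cells become rare if control abstinence is 8% or more, and markedly more common at 3%. The figures do not carry over to other time points, for which no rates are given, or to the Cox models.

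**What to change.** In **Data analysis**:
- Fit the surgery-type-by-intervention term for 12-month abstinence by Firth-penalised logistic regression, with a profile-likelihood confidence interval and test.
- Alongside it, report the 12-month risk difference in each surgery group and the difference between the two, each with a 95% CI.
- State that the two scales answer different questions if control abstinence differs by surgery type. Do not make either supplementary on grounds of power alone.

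In the **Introduction** and **Discussion**: say that only very large differences between surgery types can be detected on either scale, with the power figures above, and that a non-significant interaction does not show equal effect.

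The cost is a few lines of text, one extra model and two scales to explain. No extra patients or data are needed. With 25 subjects recruited at the time of writing (Current status of the RCT), the change can be made well before analysis.

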### Ethical considerations

The protocol for this intervention has been approved by the Vall d’Hebron University Hospital’s Drug Research and Ethics Committee [reference: PR(AG)367/2018, v2]. The study protocol has been registered at ClinicalTrials.gov, (2023) (NCT05961813). The study will be conducted in accordance with the Biomedical Research Act 14/2007 and the principles established by the World Medical Association’s 2013 Declaration of Helsinki and its subsequent amendments. The processing, communication and transfer of participants’ personal data will comply with EU Regulation 2016/679 of 27 April 2016 on Data Protection and Spanish Organic Law 3/2018 of 5 December on the protection of personal data and the guarantee of digital rights. Informed consent will be requested from all participants.

## DISCUSSION

Smoking is a major risk for patients undergoing surgery. Surgical complications are associated with smoking increasing readmission rates, prolonging hospital stays and ultimately increasing healthcare costs.

Smokers scheduled for surgery are at an ideal time to try a quit attempt^32^. Intensive interventions initiated at preoperative visits are known to be effective^17^ and can reduce complications. Despite this evidence, little help in this regard is offered during pre-surgical visits^33^. This study is the first in Spain to evaluate the effectiveness of an intensive pre-surgical intervention comprising psychological and behavioral support, pharmacological therapy, and a one-year follow-up program designed to help patients quit smoking before they undergo surgery.

The sample size and stratification will allow us to perform subgroup analyses, and the one-year follow-up period will enable us to obtain longterm abstinence data comparing CO-oximetry measurements made on the day of surgery and at the end of the study.

The main expected result is the achievement of an abstinence rate that is 15% higher among patients in the IG compared to those in the CG, and, at the same time, a reduction in the risk of complications in the IG. The analyses will also consider sociodemographic variables, comorbidities, type of surgery, and surgical variables such as duration and transfusions required. Other important results for comparison between groups will be motivation, dependence, cessation attempts, and reduction in consumption.

### Limitations

The main limitation of the study is the likely loss of subjects; however, this issue has been taken into account in the calculation of the sample size and in the inclusion criteria. In addition to the limitation of single blinding, we have identified other potential limitations in our study, such as the possibility of selection bias due to the non-random nature of certain inclusion criteria (e.g. type of surgery). However, to minimize potential selection bias, we will analyze the data stratified by type of surgery and explore the interaction between the type of surgery and the randomization group (intervention vs control). Finally, since the study is conducted in a single hospital, there is the potential of limited generalizability of the findings to broader patient populations. Nonetheless, the study is conducted at the largest hospital in Catalonia, with a potential population reach of more than 430000 inhabitants, being the reference for these surgeries in the entire region.

### Current status of the RCT

Patient recruitment began in May 2023 and currently 25 subjects have been recruited. The pace of recruitment is slow because many eligible patients decline the invitation. In view of this scenario, since the beginning of the RCT a database has been created with details of the eligible participants who refuse to participate and their reasons for use in subsequent analysis.

The RCT follows the plan of the proposed intervention closely and we hope to reach the sample size necessary, albeit more slowly than expected.

## CONCLUSIONS

If the present study demonstrates the efficacy of this opportunistic intensive intervention in smokers about to undergo surgery, it seems justified to propose its implementation in the standard clinical practices of the rest of the surgical specialties of the Catalan Health System.

## Data Availability

Data sharing is not applicable to this article as no new data was created.
